## Abstract

**Background:**

Chronic kidney disease (CKD) is considered a serious public health problem, both in Brazil and worldwide, with an increasing number of cases observed inrecent years. Especially, CKD has been reported to be highly prevalent in those of African descent. However, Brazil lacks data from early-stage CKD population studies, and the prevalence of CKD is unknown for both the overall and African descent populations. Hence, the present study aimsto estimate the prevalence of early-stage CKD and its associated risk factors in African-Brazilians from isolated African-descent communities. Herein, the detailed methodology design of the study is described.

**Methods:**

This population-based, prospective, longitudinal, cohort study (PREVRENAL) is performed in three stages: first, clinical, nutritional, and anthropometric evaluations; measurements of serum and urinary markers; and examinations of comorbiditieswere performed. Second, repeated examinations of individuals with CKD, systemic arterial hypertension, and/or diabetes mellitus; image screening; and cardiac risk assessment were performed. Third, long-term monitoring of all selected individuals will be conducted (ongoing). Using probability sampling, 1539 individuals from 32 communities were selected. CKD was defined asaglomerular filtration rate (GFR) ≤60 mL/min/1.73m^2^ and albuminuria > 30 mg/day.

**Discussion:**

This study proposes to identify and monitor individuals with and without reduced GFR and high albuminuria in isolated populations of African descendants in Brazil. As there are currently no specific recommendations for detecting CKD in African descendants, four equations for estimating the GFR based on serum creatinine and cystatin C were used and will be retrospectively compared. The present report describes the characteristics of the target population, selection of individuals, and detection of a population at risk, along with the imaging, clinical, and laboratory methodologies used. The first and second stages have been concluded and the results will be published in the near future. The subsequent (third) stage is the long-term, continuous monitoring of individuals diagnosed with renal abnormalities or with CKD risk factors. The entire study population will be re-evaluated five years after the study initiation. The expectation is to obtain information about CKD evolution among this population, including the progression rate, complication development, and cardiovascular events.

## Background

### The clinical problem

Chronic kidney disease (CKD) is considered a serious public health problem in Brazil and worldwide, with an increasing number of cases during recent years [1, 2]. Brazil still lacks data from population studies concerning early stage CKD. The available information is restricted to those from patients with stage 5 CKD, who received renal replacement therapy in dialysis units [3, 4]. Approximately 40% of the Brazilian population is of African descent, which ranks Brazil as the county with the second highest percentage of African descendants worldwide (following Nigeria). From a social-economic perspective, African descendants are poorer and less educated when compared with the overall population. Studies of this population group in other countries, primarily the United States, suggest that kidney diseases are more prevalent in those of African descent, especially CKD, when compared with other ethnic groups [5–8]. Ethnic studies also demonstrated high rates of adverse cardiovascular events [9, 10], diabetes mellitus (DM), and obesity, among other risk factors [11, 12], among this group. It is worth emphasizing that even during the early stages of CKD,with discrete decreases in glomerular filtration rate (GFR), cardiovascular diseases (CVD) are the primary causes of death [13].

### Aims of this study

The present study (PREVRENAL) aimedto estimate the prevalence of earlystage CKD and its associated risk factors in African Brazilians from isolated quilombo communities. It also aims to evaluate demographic, clinical, and laboratory aspects of this patient population, and identify factors associated with the development of CVD.

## Methods and study design

### Study location and population

This study was performed in Alcântara, Brazil, a city located on the west coast of the State of Maranhão (Northeastern Brazilian region). This city has 21,851 inhabitants, with 15,452 individuals (70.71%) from rural populations distributed among 139 isolated African-descent communities (quilombos). Ancestors of the evaluated ethnic group were from the Ivory Coast, Angola, and Mozambique. Criteria used for ethnicity definition was the same as that used by the Brazilian Geography and Statistics Institute, which adopts self-assignment, posteriorly confirmed by genetic examination.

The sample individuals of this study were selected through probability sampling, which was designed in three stages. First, there was a randomized selection of census sectors, with probabilities proportional to population sizes. Second, households were randomly selected. Third, individuals aged over 18 years old, who lived in the selected households, were included in the study sample. Total sample size was estimated per 15% CKD prevalence expectation, with 2% sampling error, and 95% confidence level, composing a minimal sample of 1224 individuals. Finally, 1539 individuals were selected from 32 quilombo communities. The following were excluded from the sample: individuals under 18 years old, pregnant women, and patients with chronic consumptive disease, hematological diseases, autoimmune diseases, infections, chronic or acute kidney diseases undergoing dialysis treatment, thyroid disease, and those using immunosuppressant drugs, based on clinical history and physical examination.

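### The minimum of 1224 for ±2 points is a simple-random-sample size with no design effect, although the sample is clustered; whether the 1539 selected reach ±2 points depends on an unstated design effect

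*Protocol article*

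**What the plan says.** All of the relevant text is in one paragraph of the protocol article, under Study location and population.

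- Sample size: "Total sample size was estimated per 15% CKD prevalence expectation", "with 2% sampling error, and 95% confidence level, composing a minimal sample of 1224 individuals".
- Design: participants were "selected through probability sampling, which was designed in three stages". At the first stage "there was a randomized selection of census sectors, with probabilities proportional to population sizes". Households were then drawn at random, and at the third stage "individuals aged over 18 years old, who lived in the selected households, were included in the study sample".
- Sample obtained: "Finally, 1539 individuals were selected from 32 quilombo communities".

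The paragraph gives no design effect, no ICC, no number of sampled sectors and no reason for the rise from 1224 to 1539. The section on statistical analysis makes baseline CKD prevalence, with its 95% confidence interval, the primary analysis.

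**The concern.** The printed minimum matches a formula for independent observations, but the design clusters people twice, by area and by household. People in the same place or household tend to resemble each other in kidney risk, so each additional person from a cluster usually adds less information than an independent draw would. The usual remedy is to multiply the simple-random-sample size by a design effect.

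This is more than a detail left out of a condensed article. The article prints the number, its three inputs and the design side by side, and the number fits only a design other than the one described.

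At stake is the planned precision of the primary estimate. The Discussion says that results will go to government bodies to support public policy, and readers there may carry away ±2 points as the accuracy of the study.

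**Working it through.** **Inputs from the article:** p = 0.15; d = 0.02; z = 1.96 (95%); stated minimum 1224; selected 1539 in 32 communities; 15,452 rural residents of all ages in 139 communities.

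**Assumed, because the article does not give them:** ICC of 0.01, 0.02 and 0.05 as a range; communities as the clusters; equal community sizes.

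**1. Reproduce the stated figure.**
n₀ = z² p(1−p) / d² = 1.96² × 0.15 × 0.85 / 0.02² = 1224.5, against 1224 stated. Applying a simple finite-population correction would give 1135 (population 15,452) or 1160 (the city's 21,851), and neither matches. So 1224 contains no design effect, no finite-population correction and no non-response allowance.

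**2. Slack at 1224.**
Half-width = 1.96 × √(0.1275 / 1224) = 2.00 points. There is none: under this formula any design effect above 1 exceeds 2 points.

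**3. Slack at 1539.**
Largest tolerable design effect = 1539 / 1224.5 = 1.257. With m = 1539/32 = 48.1 people per community and deff = 1 + (m − 1) × ICC, the largest ICC is 0.257 / 47.1 = 0.0055.

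**4. Margins without a finite-population correction.**
Half-width = 1.96 × √(0.1275 × deff / n). At 1224, m = 1224/32 = 38.25.

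| ICC (assumed) | deff at 1224 | margin at 1224 | deff at 1539 | margin at 1539 |
|---|---|---|---|---|
| 0.01 | 1.37 | ±2.34 | 1.47 | ±2.16 |
| 0.02 | 1.75 | ±2.64 | 1.94 | ±2.49 |
| 0.05 | 2.86 | ±3.38 | 3.35 | ±3.27 |

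**5. Margins with a finite-population correction.**
First-stage fraction f₁ = 32/139 = 0.230. Mean community size is 15,452/139 = 111.2, so the within-community fraction f₂ is 48.1/111.2 = 0.433 at 1539 and 38.25/111.2 = 0.344 at 1224.

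- Correcting the whole variance by the first-stage fraction only: (1 − 0.230) × (1 + 47.1 × ICC) ≤ 1.257 gives ICC ≤ 0.013 at 1539.
- Correcting both stages: deff = (1 − f₁) × m × ICC + (1 − f₂) × (1 − ICC). At 1539 and ICC 0.01 this is 0.370 + 0.562 = 0.932, so the margin is 1.784 × √0.932 = 1.72 points, where 1.784 is the margin at 1539 with deff = 1.

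| ICC (assumed) | margin at 1224, both stages corrected | margin at 1539, both stages corrected |
|---|---|---|
| 0.01 | ±1.94 | ±1.72 |
| 0.02 | ±2.22 | ±2.03 |
| 0.05 | ±2.90 | ±2.76 |

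On this basis ±2 points is kept up to an ICC of about 0.012 at 1224 and 0.019 at 1539.

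**6. If clustering acted only within households.**
The largest ICC at 1539 would be 0.257/(k − 1) for k adults per household: about 0.26 for two adults and 0.13 for three. The article gives no number of adults per household.

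**The case against.** The strongest reply is that the target is a closed, finite population. The aims concern isolated quilombo communities, and the stated limitations disclaim extrapolation to all Brazilians of African descent. If inference is to the 139 communities, a finite-population correction is legitimate and the margins shrink as in step 5. This stands, and it is why no shortfall at 1539 can be asserted. It has limits. The stated 1224 does not use such a correction. Selection proportional to size favours larger communities, which lowers the within-community fraction and weakens the correction, while counting adults only would strengthen it.

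Second, 1539 is 25.7% above 1224 and may contain an allowance for clustering or non-response that the full protocol explains. That is possible, but the article ties the 2% to 1224 and gives no reason for the increase. It also does not say whether 1539 is counted before or after the listed exclusions; any loss would use up part of the slack.

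Third, the ICCs and the choice of 32 communities as clusters are assumptions. The first-stage unit is the census sector, and the number of sectors is not given. Fewer than 32 would make the limit stricter, while purely household clustering would make it much looser. This stands.

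Fourth, the 2% is a planning input, and the prevalence will be reported with its own confidence interval. That is so, and it limits the consequence, but it does not make 1224 the right minimum for this design.

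The Discussion also calls the population homogeneous, but nowhere uses this to justify a design effect of 1.

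**Conclusion.** The point holds as a mismatch between formula and design. The arithmetic itself is right: 1224 is correct for a simple random sample. As the minimum for ±2 points under three-stage sampling it is not justified, because it leaves no room for any design effect above 1.

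A reader might go further and infer that the study cannot deliver ±2 points at 1224, or that 1539 delivers it only if clustering is almost absent. The documents support neither. With both stages corrected for the finite population, ±2 points survives up to an ICC of about 0.012 at 1224 and 0.019 at 1539. Without any correction the limit at 1539 is 0.0055. Which figure applies depends on the ICC, the number of sectors and the inference target, and the article settles none of these for the calculation.

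Over the assumed ICCs of 0.01 to 0.05, the margin at 1539 therefore runs from about ±1.7 to ±2.8 points with the correction and ±2.2 to ±3.3 without it. The point matters for how the precision of the primary estimate is described. It does not show the estimate to be biased or the sample inadequate.

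**What to change.** Do not enrol more; the article reports that the first two stages are complete. Change the text as follows.

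1. State that 1224 assumes simple random sampling.
2. Give the number of census sectors sampled, and say what the rise to 1539 was meant to cover.
3. Restate the expected margin at 1539 over a declared range of design effects, and say whether a finite-population correction is used and for which target population. Label any ICC or design effect as an assumption.
4. With the results, report the observed design effect and a design-based confidence interval for prevalence.

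The cost is a few sentences and an analysis that uses the sector and household identifiers. The downside is that the stated precision may become less favourable than ±2 points.

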### Study design and summary

This was a cohort study with the following characteristics: population based, prospective, longitudinal, and performed in three stages (Fig. 1). In the first stage, clinical, nutritional, and anthropometric evaluations, measurements of serum and urinary markers for CKD, and examinations for comorbidities (systemic arterial hypertension [SAH], DM, CVD, obesity, and dyslipidemia) were performed. The second stage consisted of repeated examination of individuals with CKD, SAH, and/or DM, image screening, and cardiac risk assessment. The third stage included long-term monitoring of all selected individuals.

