### First stage

#### Data collection

A questionnaire was completed for each adult in each household. Individual questionnaires were divided into blocks with the following subjects: basic demographic information (age, gender, marital status, and migration); socioeconomic characteristics (education, occupation, working relationship, and income); personal habits (smoking, alcoholism, diet type, and physical exercises); clinical data; arterial blood pressure(AP) status; previous disease of the cardiovascular, renal, and respiratory systems; medications; and health services usage. A minor diet survey was conducted in each family (including sodium content) by nutritionists.

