### Statistic analysis

First, a descriptive analysis of the variables under study will be performed. Quantitative variables will be presented by mean and standard deviation and qualitative variables by frequencies and percentages. The Shapiro Wilk test will be used to evaluate the normality of the quantitative variables.

For categorical variables, group comparison will be based upon the results of the Chi-square test. Chi-square test will be replaced by Fisher’s exact test if the expected frequency in any of the cells of the contingency table is less than 5. For continuous variables, group comparison will be based upon the results of the *t*-test or the Wilcoxon rank-sum test, depending on the normality.

In the primary analysis, the prevalence of CKD at baseline and its corresponding 95% confidence interval (CI) will be presented. Prevalence of hypertension, diabetes mellitus, cardiovascular disease and other comorbidities at baseline and their corresponding 95% CIs will also be presented.

In the secondary analysis, the factors associated with the presence of CKD through bivariate analysis with an unadjusted prevalence ratio estimate and a 95% confidence interval (95% CI) will be used. The independent variables that present a significance lower than 0.20 (*p*-value < 0.20) will be considered in the final model, that is, in the adjustment of potentially confounding variables through the multivariate logistic regression technique performed step by step.

The comparison of survival (based on all-cause mortality) between patients with and without CKD will also be performed based upon the log-rank test performed at a significance level of 0.05. Hazard ratios and 95% CIs will be calculated by a Cox proportional hazard regression model.

The data will be analyzed in the statistical program STATA 12.0.

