## Discussion

Brazil lacks early-stage CKD population study data. The prevalence of CKD in our country is unknown for both the overall and African descent populations. After identifying individuals with reduced GFR and high albuminuria, in an isolated population of African descendants, this study proposes to monitor patients with or without these conditions during long-term follow-up. This study also seeks to identify other associated clinical conditions, including SAH, DM, anemia, dyslipidemia, metabolic syndrome, and cardiovascular risk. There are no specific recommendations for detecting CKD in African descendants [26, 27], thus four equations for estimating GFR based on serum creatinine and cystatin were used and will be compared.

To date, there are no reports on arteriosclerotic disease and its relationship with GFR among Brazilian African descendants. Data concerning clinical and laboratory factors related to the development of arteriosclerosis among individuals with impaired renal function during pre-uremia stages and understanding of thisprocess’ development will allow the adoption of therapeutic and preventive measures that enable reduction of cerebrovascular and coronary events, which result in high morbidity and mortality among this group of patients. Additionally, our study is the first to quantify and evaluate factors associated with coronary calcification in African descendants who descend from African slaves and live in isolated Brazilian communities, filling a gap of this research area.

Differences in CVD occurrence among ethnic groups cannot be completely explained by traditional risk factors, even when taking into account the increased rate ofSAH and DM among African descendants [28]. Thus, the association between arteriosclerosis and CKD among the various ethnic groups and impacts of risk factors on this association are not well-established. Therefore, the American Heart Association has recommended investigations of arteriosclerotic CVD among all ethnic groups, including long- and short-term risk analyses, in order to fill this knowledge gap [29].

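### The disease exclusions restrict the CKD prevalence estimate to adults free of the listed conditions, but the plan presents it as the prevalence of the whole community

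*Protocol article*

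**What the plan says.** The Abstract and Aims of this study set the target as early-stage CKD prevalence, with its risk factors, among African Brazilians living in isolated quilombo communities. Study design and summary describes the study as "population based, prospective, longitudinal, and performed in three stages". Sampling runs from census sectors to households to adults: "individuals aged over 18 years old, who lived in the selected households, were included in the study sample".

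The same section, Study location and population, then takes out under-18s, pregnant women and people with "chronic consumptive disease, hematological diseases, autoimmune diseases, infections, chronic or acute kidney diseases undergoing dialysis treatment, thyroid disease, and those using immunosuppressant drugs". These exclusions were applied "based on clinical history and physical examination", and no reason is given for them.

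CKD diagnosis counts a person as having CKD on reduced GFR and/or raised albuminuria, with no condition on cause. Statistic analysis names the main result: "In the primary analysis, the prevalence of CKD at baseline and its corresponding 95% confidence interval (CI) will be presented". It names no restricted population. The Discussion lists four limitations. The one on generalisability concerns extension to other Brazilians of African descent, and none mentions the exclusions.

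**The concern.** A prevalence estimate belongs to the population from which the analysed people come. Here a probability sample of community adults is filtered on health status, while the outcome is defined without regard to cause. The result is then labelled as if the filter had not been applied. If the removed adults have a different CKD prevalence from those kept, the published figure is wrong for the population it names. A larger sample does not cure this, and the confidence interval does not reflect it, because it is not sampling error.

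The article says results will go to the government bodies that manage the public health system. Those readers would naturally take the figure as the prevalence among all adults of these communities.

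**Working it through.** **Inputs from the article.** Expected prevalence 15%, sampling error 2 points, 95% confidence, minimum sample 1224, selected sample 1539 (Study location and population). The number excluded for disease and the CKD prevalence among them are not given. It is also not stated whether 1539 is counted before or after exclusions, so the share excluded cannot be worked back. Figure 1 is not shown and may hold counts.

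**Step 1: the plan's own figure.** n = z² p(1−p)/d² = 1.96² × 0.15 × 0.85 / 0.02² = 1224.5, which agrees with the stated 1224. With 1539 people, the half-width under simple random sampling is 1.96 × √(0.15 × 0.85/1539) = 1.78 points. The sample size is not affected by this point. It only gives a yardstick of about 2 points.

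**Step 2: the identity.** Let e be the share of sampled adults excluded, P_kept the prevalence among those kept and P_excl the prevalence among those excluded. Then

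- P_all = (1−e) × P_kept + e × P_excl
- shift = P_all − P_kept = e × (P_excl − P_kept)

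The reported figure understates P_all only if P_excl exceeds P_kept.

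**Step 3: assumed values, with P_kept = 15%.** The values of e and P_excl are assumptions chosen to show the range.

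| e | P_excl | P_all | Shift (points) |
|---|---|---|---|
| 2% | 45% (3 times) | 0.98 × 15 + 0.02 × 45 = 15.6% | +0.6 |
| 5% | 30% (2 times) | 0.95 × 15 + 0.05 × 30 = 15.75% | +0.75 |
| 5% | 45% (3 times) | 0.95 × 15 + 0.05 × 45 = 16.5% | +1.5 |
| 10% | 30% (2 times) | 0.90 × 15 + 0.10 × 30 = 16.5% | +1.5 |
| 10% | 45% (3 times) | 0.90 × 15 + 0.10 × 45 = 18.0% | +3.0 |
| 10% | 15% (equal) | 15.0% | 0 |
| 10% | 10% (lower) | 0.90 × 15 + 0.10 × 10 = 14.5% | −0.5 |

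**Step 4: when the shift matches the planned margin.** Setting e × (P_excl − 0.15) = 0.02 gives e = 0.02/(P_excl − 0.15). That is 40% excluded if P_excl is 20%, 13.3% if 30%, 6.7% if 45% and 4.4% if 60%.

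The shift is therefore minor when few are excluded or the two groups are alike. It exceeds the planned margin only when a sizeable share is excluded and their prevalence is much higher.

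**The case against.** The strongest reply has four parts.

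- **Measurement.** GFR is estimated from creatinine and cystatin C. Some excluded conditions may disturb these markers, and an infection may raise them only for a time, so including such people could misclassify CKD. This is a fair reason to set their results aside, although the article does not give it. It does not make the remaining sample represent everyone.
- **Size.** Exclusion rested on history and physical examination, so only known or clinically evident disease was removed. The share may be small. With up to 5% excluded and up to 30% prevalence among them, the shift is at most 0.75 points. This stands as a possibility, but the article gives no count to confirm it.
- **Format.** A journal article may leave exclusion counts and sensitivity analyses to the full protocol or analysis plan. Their absence is accordingly not the fault raised here. What stands is that the article itself states a target, a set of exclusions, a primary result and a list of limitations, and these do not fit together.
- **Dialysis.** Leaving out dialysis patients fits the early-stage aim and is not criticised.

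A reader might go further and infer that the primary estimate is biased downward as a matter of fact, because autoimmune disease, haematological disease and immunosuppressant use are associated with kidney damage. The documents do not support that as a finding. They give neither quantity that fixes the sign, and they state no such link. The same list includes thyroid disease, chronic consumptive disease and infections, and pregnancy is excluded alongside it. No direction is shown for any of these.

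**Conclusion.** The mismatch between target and sample holds on the text alone. As planned, the primary estimate is the CKD prevalence among adults free of the listed conditions, but it is presented as that of the communities. Downward error is plausible but not established. On the assumptions above (15% among those kept, three times that among the excluded), the shift is 0.6, 1.5 or 3.0 points at 2%, 5% or 10% excluded. It vanishes or reverses if the excluded have equal or lower prevalence. The true size cannot be computed from the documents.

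Two further inferences should not be drawn:

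- The Discussion aims to identify conditions "including SAH, DM, anemia, dyslipidemia, metabolic syndrome, and cardiovascular risk", so a reader might think anaemia prevalence is cut at entry. That requires known anaemia to have been treated as a haematological disease, which the article does not say. Haemoglobin is among the first-stage tests.
- A reader might also look to the five-year re-visit for a remedy. That stage already plans to return to everyone selected for the first stage and states no new exclusion. It cannot repair the baseline figure.

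**What to change.** - In Statistic analysis, and wherever the result is stated, define the primary estimate as CKD prevalence among adults without the listed conditions.
- Report the number of sampled adults excluded for each reason, as far as this was recorded when history and examination were taken. Data collection says "A questionnaire was completed for each adult in each household", but it does not say that excluded adults are covered, so this source needs checking before it is relied on. Nothing shows that GFR or albuminuria was measured in them.
- Add a sensitivity estimate of all-adult prevalence, (1−e) × P_kept + e × P_excl, over a stated range for P_excl that includes values below P_kept, so that the direction is not fixed in advance.
- Add the exclusions to the limitations in the Discussion.

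The cost is some rewording and one short table, with no new participants or tests. The price in interpretation is a narrower claim for the headline figure, or a wider stated range for the whole community. If counts by reason were not kept, e must also be given as an assumed range.
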